**Figure 3 F3:**
[figure not shown]
Demonstration of the gating strategy used to characterise microparticles. (A) ‘All microparticles’ set using beads of known size. (B) ‘All microparticles’ based on Annexin-v expression. (C) Phenotype marker expression, used to quantify microparticles of different cellular sources. (D) Prothrombotic potential, assessed by Tissue Factor expression. All gates have been appropriately sized and positioned using unstained samples to distinguish negative versus positive staining. FITC, fluorescein isothiocyanate; F/SSC-H, Forward/Side Scatter-Height; PE phycoerythrin.

### Saliva sampling and storage

Saliva samples will be collected into sterile plastic containers. Participants will swallow to empty the mouth, then open and hold the container themselves before performing a passive dribble of saliva collected under the tongue over the next 2 min. Following centrifugation, the supernatant will be aliquoted and frozen for future analysis, primarily for secretory IgA to investigate mucosal immunity.

### Anthropometric measures

Height, weight and waist and hip circumference will be measured using standard procedures.^46^

### Body composition

Body composition parameters (ie, fat and fat-free mass content) will be measured using bioelectrical impedance analysis (BIA) (Inbody 370, Chicago, Illinois, USA). BIA has been validated for use in CKD.^47^ While BIA has limitations with regards to reliability and is not recommended for tracking changes in body composition, body composition will only be used as a descriptive rather than an outcome variable, and thus BIA has been deemed suitable to assess body composition for this reason.

### Cardiovascular condition and function

Cardiac bioreactance analysis will be carried out using a Non-Invasive Cardiac Output Monitor (Cheetah Medical, Maidenhead, UK). Cardiac bioreactance is a quick, safe, validated^48^ and non-invasive method of assessing central haemodynamics including heart rate, stroke volume, cardiac output and total peripheral resistance. This is accomplished by using cutaneous electrodes placed on the chest in combination with an automatic sphygmomanometer to measure blood pressure.

### Time spent in leisure activities

The Leisure Time Exercise Questionnaire assesses the amount of exercise a patient undertakes, from which a metabolic equivalent estimation can be calculated. It also identifies preferred physical activities.

### Fatigue

Fatigue is a common complaint CKD, and it has multiple potential mechanisms including anaemia^49^ and cachexia.^50^ To assess self-reported fatigue, participants will be asked to fill in a fatigue scale (an internally designed Likert scale see online supplementary material), as well as the validated Functional Assessment of Chronic Illness Therapy-Fatigue^51^ which has been extensively used in CKD populations^52^

10.1136/bmjopen-2016-014713.supp1Supplementary material 1

### Muscle O_2_ saturation

Reduced muscle O_2_ saturation is another possible physiological mechanism of fatigue^53^ and may be related to increased inflammation.^54^ A small non-invasive muscle O_2_ saturation device (BSXInsight, BSXAthletics, Texas, USA) will be fitted around the participant’s calf and worn during exercise bouts and subsequent recovery. This device uses near infrared spectroscopy (NIRS) to measure haemoglobin and myoglobin oxygenation (muscle O_2_ tissue stores). NIRS has previously been used in a variety of disease conditions.^55^

### Clinical information

Clinical records will be used to extract information that allows associations to be made with physical activity levels and account for confounding variables, including: age, gender, ethnicity, primary cause of renal failure, transplant or dialysis type, time since transplant or duration of dialysis, comorbidities and current medications.

### Data analysis plan

Mixed-design analyses of variance will be used to analyse main effects of group and time and interaction effects, with Bonferroni post hoc testing used to elucidate these effects. This will generate both tests of significance and estimates of effect sizes. Any non-normally distributed data will first be transformed appropriately to ensure normality assumptions are met, to increase statistical power and to allow clear conclusions to be drawn from the data. Where normality assumptions cannot be met via data transformation, Friedman’s tests will be employed as a non-parametric alternative. This will allow the generation of hypotheses for future, larger studies.

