**Methods and analysis:**

Patients with CKD, including renal transplant recipients, will visit the laboratory on two occasions, both preceded by appropriate exercise, alcohol and caffeine restrictions. On visit 1, baseline assessments will be completed, comprising anthropometrics, body composition, cardiovascular function and fatigue and leisure time exercise questionnaires. Participants will then undertake an incremental shuttle walk test to estimate predicted peak O_2_ consumption (VO_2_peak). On visit 2, participants will complete a 20 min shuttle walk at a constant speed to achieve 85% estimated VO_2_peak. Blood and saliva samples will be taken before, immediately after and 1 hour after this exercise bout. Muscle O_2_ saturation will be monitored throughout exercise and recovery. Age and sex-matched non-CKD ‘healthy control’ participants will complete an identical protocol. Blood and saliva samples will be analysed for markers of inflammation and immune function, using cytometric bead array and flow cytometry techniques. Appropriate statistical tests will be used to analyse the data.

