### Participant recruitment

All patients with CKD attending outpatient clinics within the University Hospitals of Leicester renal network will be screened for eligibility by their consultant nephrologist prior to recruitment, and approached during their routine outpatient appointments. The inclusion and exclusion criteria for patients are summarised in table 1. Healthy age-matched and sex-matched controls with no known chronic disease will be recruited from the local community. Those who do not believe themselves to suffer from any significant chronic disease will be eligible to participate. The ‘broad’ inclusion and exclusion criteria allow the incorporation of several different groups (ie, patients with non-dialysis CKD, with dialysis, RTRs and healthy controls), and thus will allow comparison between these groups. Similarly, the wide range of CKD stage will allow the influence of remaining renal function on the measured markers to be investigated.

**Table 1 T1:** Inclusion and exclusion criteria for patients

Inclusion criteria	Exclusion criteria
Established chronic kidney disease (all stages will be eligible including those with an established kidney transplant and those receiving dialysis treatment)	Age under 18 years Pregnancy Received kidney transplant less than 6 months prior to study entry Any element of study assessment protocol considered by principle care provider to be contraindicated due to physical impairment, comorbidity or any other reason Inability to give informed consent for any reason Visual or hearing impairment or insufficient command of English to give informed consent or comply with the assessment protocol

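### The only stated model contains group and time, so the promised confounder adjustment and renal-function question have no analysis, and its classical form uses only complete sample sets

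*Protocol article*

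**What the plan says.** The Data analysis plan of the protocol article fixes one model: "Mixed-design analyses of variance will be used to analyse main effects of group and time and interaction effects", followed by Bonferroni post hoc tests. Its fallback is: "Where normality assumptions cannot be met via data transformation, Friedman’s tests will be employed as a non-parametric alternative". It names no covariate and gives no rule for a missing sample.

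Three other places bear on this:

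- **Clinical information** says records will be used to "account for confounding variables, including: age, gender, ethnicity, primary cause of renal failure, transplant or dialysis type", and the list goes on to comorbidities and medications.
- **Participant recruitment** says "the wide range of CKD stage will allow the influence of remaining renal function on the measured markers to be investigated". It also intends comparisons between non-dialysis, dialysis, transplant and control groups. On design control it says: "Healthy age-matched and sex-matched controls with no known chronic disease will be recruited from the local community".
- **The abstract** sets the repeated measures: "Blood and saliva samples will be taken before, immediately after and 1 hour after this exercise bout".

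Trial design and timeline calls the study non-randomised. Under Visit 1, anyone who cannot finish the 20-minute walk is withdrawn.

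**The concern.** Two stated intentions have no analysis behind them. A group-by-time ANOVA without covariates cannot account for ethnicity, comorbidities or medications, and it cannot relate a marker to eGFR. Friedman's test takes neither a covariate nor a between-group factor. Because the groups are not randomised, a difference in level between them could reflect who is in each group rather than kidney disease.

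A second, smaller issue lies in the method. Classical mixed-design ANOVA and Friedman's test need a complete set of three samples from each participant. Lost samples are plausible here. There are repeated 30 mL venepunctures with fistula arms excluded, one draw is due within 5 minutes of exercise, and immune cells are run on the day of collection. With about 15 per group, losing a whole participant for one failed sample matters. The article also says the study will supply data for the power calculation of a larger trial, so unadjusted group effects and imprecise estimates would carry forward.

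**Working it through.** **The plan's own figure.** The Introduction gives 15 per group at power 0.80 and alpha 0.05, based on total lymphocyte count. It states no effect size, SD, within-person correlation or test, so 15 can be neither reproduced nor refuted. For orientation, a two-sample t test with 15 per group has 80% power at a standardised difference of about 1.06.

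**What is promised against what is modelled**

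| Stated intention | Where | Carried by the stated analysis? |
|---|---|---|
| Compare groups, times and their interaction | Data analysis plan | Yes (ANOVA); Friedman covers time only |
| Account for confounders | Clinical information | No covariate named |
| Investigate remaining renal function | Participant recruitment | No eGFR term or model |
| Age and sex balance, patients v controls | Participant recruitment | By matching, not by the model |
| Balance between patient subgroups | – | No matching or adjustment described |

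**Size of the confounding.** The inputs are assumptions: 15 v 15, three times, and a confounder that shifts the level of the outcome only. The expected bias in the group main effect is imbalance (in SD of the confounder) × slope. Simulation gave:

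| Imbalance, slope | Bias, unadjusted | Type I error, unadjusted | Adjusted | Group × time |
|---|---|---|---|---|
| 0, 0.4 | 0.01 | 4% | 5% | 5% |
| 0.3, 0.4 | 0.11 | 6% | 5% | 5% |
| 0.5, 0.4 | 0.21 | 9% | 5% | 5% |
| 1.0, 0.4 | 0.39 | 22% | 5% | 5% |

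With slope 0.2, the unadjusted error is about 6% at imbalance 0.5 and 11% at 1.0. The harm falls on the group main effect. The group-by-time contrast keeps its 5% as long as the confounder does not change the response to exercise.

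**Size of the complete-set loss.** Assume that each sample is missing independently with probability p, completely at random. Write q = 1 − p.

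- Participants with all three samples: q³. For p = 5%, 0.95³ = 0.857, so 14% are lost (15 × 0.143 ≈ 2 per group). For p = 10%, 0.90³ = 0.729, so 27% are lost (15 × 0.271 ≈ 4 per group).
- Variance of a change from baseline, complete sets relative to full data: 1/q³ = 1.17 and 1.37.
- The same variance for a mixed model on all samples, with compound symmetry and within-person correlation 0.5 (assumed). The average information per participant has diagonal a = 1.5q³ + (8/3)q²p + qp² and off-diagonal b = −0.5q³ − (2/3)q²p. The change has variance 2/(a − b), against 1 for full data.
  - p = 5%: a = 1.409, b = −0.459, and 2/1.868 = 1.07.
  - p = 10%: a = 1.3185, b = −0.4185, and 2/1.737 = 1.15.
- Power, starting from 80% (normal approximation): Φ(2.80/√variance − 1.96).

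| p | Complete sets | Mixed model | Avoidable loss |
|---|---|---|---|
| 5% | 0.737 | 0.773 | 3.6 points |
| 10% | 0.667 | 0.743 | 7.5 points |

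With correlation 0.3 or 0.7 in place of 0.5, the avoidable loss is 3.4 to 3.8 points at 5% missing and 7.1 to 8.0 points at 10%.

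**The case against.** The strongest reply is that this is a hypothesis-generating feasibility study about the response to acute exercise. That response rests on time and group-by-time contrasts, for which mixed-design ANOVA is a standard, valid analysis. Much of this stands, and several stronger readings should be set aside.

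- *That the plan drops anyone missing a sample.* The article does not say so. Deletion follows from the classical form of the methods it names, and a missing-data rule may sit in a full protocol or analysis plan that is not shown. The absence of such a rule is not the criticism.
- *That the plan promises to adjust for renal function.* It does not. Renal function is not on the confounder list; its influence is to be investigated. It largely defines patient against control, so adjusting that contrast for it would remove part of the effect of interest.
- *That age and sex are left uncontrolled, or cannot be matched.* Controls are matched on both. The article describes no matching between patient subgroups and no re-matching after withdrawals, but residual imbalance is possible rather than shown.
- *That the whole fall from 80% power is due to the ANOVA.* A mixed model loses precision too, so only the difference counts. It also recovers nothing from people withdrawn at visit 1, who give no visit 2 samples.

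It is also fair that much of the confounder list describes patients only, and that adding age and sex leaves the unmatched confounders unadjusted. The reply does not remove the mismatch: the article says confounders will be accounted for and renal function investigated, and the analysis it fixes does neither.

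**Conclusion.** The concern holds in a limited form. The stated analysis carries out neither intention, so group main effects and contrasts between patient subgroups stand unadjusted. Under assumed imbalances of 0.5 to 1.0 SD with slope 0.4, type I error for the group main effect would be 9% to 22%; with small imbalance it stays near 5%. Time and group-by-time results are largely safe from confounders that act on level alone, so a reader should not conclude that the exercise findings as a whole are confounded.

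The named methods also waste samples in their classical form. The avoidable cost is modest, about 3 to 8 points of power, and it depends on assumed missing rates of 5% to 10%, missingness at random and within-person correlation of 0.3 to 0.7. The article gives none of these figures. The change is worth making because it uses data already being collected.

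**What to change.** 1. Replace the ANOVA with a linear mixed model (REML, Kenward-Roger) on all available samples, with group, time, group by time, age and sex. Keep the Bonferroni contrasts and report adjusted differences with 95% confidence intervals.
2. State that the unmatched confounders (ethnicity, comorbidities, medications) are too many to fit together at about 15 per group, and that they limit interpretation of the group main effects.
3. Answer the renal-function question with a separate model in non-dialysis patients and transplant recipients, containing eGFR and eGFR by time. Do not adjust the patient–control contrast for eGFR.

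The cost is two covariate degrees of freedom and slightly more analysis work. No new data are needed: age and sex are recorded, and eGFR is measured in patients and controls.

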In the CKD population, similar positive effects of exercise on body composition, physical function and quality of life have been demonstrated^30–33^; however, the research on inflammation and immune function in this population is limited. Previous research has shown that 30 min of moderate intensity walking exercise elicited a normal pattern of leucocyte and monocyte activation, while enhancing granulocyte function and promoting an anti-inflammatory environment (increased IL-10 release) in patients with pre-dialysis CKD.^34^ However, in a similar population, an exhaustive bout of cycling exercise elicited a shift towards the more proinflammatory CD16^+^ monocyte, potentially favouring inflammation.^35^ This disparity may be due to the exercise intensities investigated—moderate intensity exercise is more beneficial in strengthening immune function and preventing infection^26^ and is promoted in general exercise guidelines. As such, investigating the effects of moderate intensity exercise in this patient population is more pragmatic and will help to guide future exercise recommendations, which are lacking in this patient population.

Therefore, this feasibility study aims to investigate the effects of acute aerobic walking exercise on the inflammation and immune function in patients with CKD. This will create the basis from which a larger trial can be conducted, including data for a power calculation, which will ultimately help to inform exercise recommendations in this population which are currently lacking, particularly with regards to immune function and inflammation.^36^ However, a preliminary power calculation (GPower V.3.1) based on the findings of Viana *et al*^34^ concerning total lymphocyte count (based on a statistical power of 0.80 and an alpha level of 0.05) suggests that 15 participants per group (eg, predialysis CKD, RTRs and healthy controls) will be sufficient.

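### Post hoc testing is fixed as plain Bonferroni; Holm's step-down on the same comparisons keeps the same 0.05 family-wise bound and never rejects less (a low-severity efficiency gain, not an error)

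*Protocol article*

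**What the plan says.** The protocol article's Data analysis plan sets the model: "Mixed-design analyses of variance will be used to analyse main effects of group and time and interaction effects". The same sentence continues "with Bonferroni post hoc testing used to elucidate these effects". No section mentions a step-down or any other multiplicity procedure.

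Three other statements set the scale of the problem.

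- **Time points.** The Abstract gives three: "Blood and saliva samples will be taken before, immediately after and 1 hour after this exercise bout".
- **Sample size.** The Introduction reports a preliminary calculation "based on a statistical power of 0.80 and an alpha level of 0.05", made "concerning total lymphocyte count", which concludes that "15 participants per group (eg, predialysis CKD, RTRs and healthy controls) will be sufficient".
- **Purpose.** The Data analysis plan closes by saying "This will allow the generation of hypotheses for future, larger studies". It also gives greater power as one reason for transforming non-normal data.

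**The concern.** Bonferroni holds every comparison to alpha divided by the number of comparisons, however many of the others have already been rejected. Holm starts at that same threshold and relaxes it after each rejection. For accept-or-reject decisions at a fixed family-wise bound, plain Bonferroni is therefore dominated by a procedure that uses the same p-values and needs no extra assumption about their correlation.

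What is at stake is modest. With about 15 people per group, a real change that narrowly misses the Bonferroni threshold would be reported as not significant when Holm could have declared it at the same bound. That sits awkwardly with a plan that mentions statistical power as a goal and is meant to generate hypotheses.

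**Working it through.** **Inputs from the document.** There are 15 per group, alpha 0.05 and power 0.80 (Introduction), and three sampling times (Abstract; Visit 2). Three times give 3 × 2 / 2 = 3 pairwise time contrasts.

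**Inputs assumed.** Tests are two-sided. The effect is the one that gives a single contrast 0.80 power unadjusted at n = 15. The stated 15 per group cannot be reproduced, because the article gives neither the effect size nor the standard deviation nor the test used. The effect is therefore solved backwards from n. Contrasts are tested directly, without first requiring a significant overall F test.

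**Step 1: the two rules.** Order the p-values p(1) ≤ p(2) ≤ p(3), with m = 3.

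- Bonferroni rejects each p ≤ 0.05/3 = 0.0167.
- Holm rejects p(1) if ≤ 0.05/3 = 0.0167, then p(2) if ≤ 0.05/2 = 0.025, then p(3) if ≤ 0.05/1 = 0.05, stopping at the first failure.

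Holm's first threshold equals Bonferroni's and the later ones are larger, so every Bonferroni rejection is also a Holm rejection.

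Error control: suppose m0 of the m hypotheses are true. When Holm first reaches a true one, at most m − m0 hypotheses have been rejected, so its threshold is at most 0.05/m0. The chance that any of m0 true hypotheses has p ≤ 0.05/m0 is at most m0 × 0.05/m0 = 0.05, whatever the correlation.

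**Step 2: what adjustment costs one contrast.** Power is P(|T| > t(1 − a/2, df)), where T is noncentral t.

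- Paired: standardised change 0.778, df 14, noncentrality 0.778 × √15 = 3.013. Power is 0.80 at a = 0.05 and 0.621 at a = 0.0167.
- Two-sample: standardised difference 1.060, df 28, noncentrality 1.060 × √7.5 = 2.902. Power is 0.80 at a = 0.05 and 0.640 at a = 0.0167.

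**Step 3: Bonferroni against Holm on the same simulated data** (n = 15 per group, three comparisons, 40,000 runs, within-person correlation 0.5).

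| Scenario | Power per real contrast, Bonferroni → Holm | All real contrasts found | At least one found |
|---|---|---|---|
| Time: rise, back to baseline at 1 h | 0.62 → 0.66 | 0.45 → 0.54 | 0.79 both |
| Time: rise, then equal fall below baseline (each change from baseline) | 0.62 → about 0.77 | 0.34 → 0.61 | 0.999 both |
| Time: rise, half lost by 1 h (average of three) | 0.31 → 0.34 | 0.006 → 0.033 | 0.66 both |
| Group difference at each of three times, only one real | 0.64 → 0.64 | 0.64 both | 0.64 both |

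A separate simulation with correlation 0.7 and 60,000 runs gave 0.622 → 0.663 for the first row and 0.622 → 0.774 for the second.

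The second row gains most because the post-exercise to 1 h contrast is twice the assumed effect. It is almost always rejected (0.999), which frees the 0.025 threshold for the other two.

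**Step 4: family-wise error.** Under the complete null it was 0.044 for both methods. In the rise-and-return case, where baseline against 1 h is truly null, it was 0.017 for Bonferroni and 0.034 for Holm. No simulated dataset had a Bonferroni rejection that Holm missed.

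**The case against.** The case for leaving the text alone is substantial.

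- **Bonferroni is valid and customary after a mixed analysis of variance.** This stands: nothing in the Data analysis plan is misstated.
- **The usual gain is small.** This stands. In the rise-and-return case adjustment costs 0.80 − 0.62 = 0.18 and Holm returns 0.66 − 0.62 = 0.04 of it. The larger gain, 0.77 − 0.62 = 0.15, needs a marker that falls as far below baseline as it rose.
- **Equal error rates are true only of the bound.** This stands. Below 0.05 the two methods' actual rates differ when some nulls are true.
- **Bonferroni comes with matching simultaneous intervals, and the plan also wants effect sizes.** This stands as a cost of the change. Point estimates do not depend on the adjustment.
- **With only the two groups named under Outcomes to be measured, the group main effect needs no post hoc test.** This stands. The point then concerns time and interaction contrasts.

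Three stronger readings are tempting but unsupported.

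- A reader might infer that every pair of group-by-time cells will be tested, with a severe loss of power. The document does not say so. Moreover, the gap between Bonferroni and no adjustment is not power that Holm recovers.
- A reader might infer that the plan must name a shorter list of contrasts. Listing them is commonly left to the full plan. Nor is a chosen list certain to help: two changes from baseline plus between-group differences in each already make four contrasts, more than the three pairwise time contrasts.
- A reader might infer that markers will be carried into the larger trial according to post hoc significance. The stated uses are data for a power calculation, effect-size estimates and hypothesis generation.

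**Conclusion.** The point holds as a low-severity efficiency improvement. That Holm rejects at least as much as Bonferroni within the same 0.05 bound is a mathematical fact and does not depend on the number of groups, the family or the correlation.

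The size of the gain does depend on assumptions. With 15 per group, three time contrasts and 0.80 unadjusted power for the assumed change, it is about 4 points per contrast for a rise and return, and about 15 points for a rise followed by an equal fall below baseline. It is essentially nil when a single contrast is real. The chance of finding at least one difference is the same under either method. The document supplies no effect size against which to choose among these scenarios.

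**What to change.** In the Data analysis plan, replace the Bonferroni wording with *Holm-adjusted (step-down Bonferroni) post hoc testing*, applied to the same comparisons. Add that Bonferroni simultaneous or unadjusted confidence intervals, labelled as such, will be reported beside the adjusted p-values.

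The change costs one sentence and requires no further data, visits or participants. Its one drawback is that the intervals may not match the Holm decisions exactly: a contrast rejected by Holm can have a Bonferroni interval that includes zero, and an unadjusted interval can exclude zero where Holm does not reject. The label should make that clear.

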## Methods and analysis

### Outcomes to be measured

This study will investigate the effect of 20 min of moderate intensity walking exercise on immune cell subsets and inflammatory markers. Participants will be grouped based on their status (ie, ‘patient’ or ‘healthy control’). Both groups will complete an identical acute, cross-sectional study protocol necessitating two study visits, as explained below.

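### For outcomes that stay non-normal after transformation, the only named fallback, Friedman's test, covers the time effect but not the group difference or the group-by-time interaction

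*Protocol article*

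**What the plan says.** The Data analysis plan of the protocol article states the main method: "Mixed-design analyses of variance will be used to analyse main effects of group and time and interaction effects". It then gives a two-step rule for non-normal outcomes. First, "Any non-normally distributed data will first be transformed appropriately to ensure normality assumptions are met". Second, if that fails, "Where normality assumptions cannot be met via data transformation, Friedman’s tests will be employed as a non-parametric alternative". No other non-parametric method is named anywhere in the article.

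The design has one between-participant and one within-participant factor. Under Outcomes to be measured, participants are classed as patients or healthy controls. Under Participant recruitment, the broad eligibility criteria admit non-dialysis, dialysis, transplant and control participants and "thus will allow comparison between these groups". The Abstract gives the time factor: "Blood and saliva samples will be taken before, immediately after and 1 hour after this exercise bout". The Introduction's preliminary power calculation "suggests that 15 participants per group (eg, predialysis CKD, RTRs and healthy controls) will be sufficient".

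**The concern.** The mixed ANOVA answers three questions: whether groups differ, whether values change over time, and whether the change differs between groups. A replacement for that analysis should answer the same three. Friedman's test is a one-way repeated-measures rank test with no between-participant factor, so it can answer only the second.

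Any outcome that reaches the fallback would lose the comparison for which the matched controls were recruited. The study is meant to supply effect estimates, a power calculation and hypotheses for a larger trial. A difference in response that went untested here would be missing from that later design.

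**Working it through.** **Inputs from the article.** Three time points (k = 3); two groups in the basic classification; 15 per group; power 0.80 and alpha 0.05.

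**The plan's own figure.** The 15 per group cannot be reproduced, because no effect size or SD is given. Solving backwards for two means, two-sided, by the normal approximation: d = √(2/15) × (1.960 + 0.842) = 0.365 × 2.802 = 1.02. This cannot be checked against the article. The point does not depend on it; 15 serves only as the simulation size.

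**Step 1: what the statistic can see.** Each participant's three values are ranked 1 to 3, so every participant's ranks sum to 6 whatever their level. With R_j the rank total at time j over N participants,

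Q = 12 / (N k (k+1)) × ΣR_j² − 3N(k+1).

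For N = 30 and k = 3 this is ΣR_j²/30 − 360. Multiplying every value in one group by a constant changes no within-person rank, so Q cannot move. A numerical check with one group multiplied by 100 gave Q = 4.467 before and after.

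**Step 2: an exact example of interaction.** Let all 15 patients rank (1, 3, 2) across the three times and all 15 controls rank (3, 1, 2).
- Pooled: each R_j = 60, so Q = 3 × 3600/30 − 360 = 0.
- Patients alone (N = 15, Q = ΣR_j²/15 − 180): totals 15, 45 and 30, so Q = 3150/15 − 180 = 30. This is the maximum, N(k−1) = 30. Controls alone give the same.

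Perfectly opposite responses therefore give a pooled statistic of exactly zero.

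**Step 3: simulation.** Assumed, not from the article: log-normal outcomes, participant SD 0.7 and residual SD 0.7 on the log scale (correlation 0.49/0.98 = 0.5, total SD √0.98 = 0.99, so one log unit is about 1 SD), any time effect at the second sample only, 4,000 runs.

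| Truth | Pooled Friedman rejects | Between-group rank comparator |
|---|---|---|
| No effects | 5.5% | 4.8% (Mann-Whitney on participant means) |
| Group shift 1.0 | 5.3% | 86.7% (same) |
| Group shift 2.0 | 5.5% | 100.0% (same) |
| Opposite responses, +0.8 and −0.8 | 2.2% | 95.3% (Mann-Whitney on change) |
| Same response, +0.6 in both | 82.8% | 4.6% (Mann-Whitney on change) |

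The Monte Carlo standard error near 5% is √(0.05 × 0.95/4000) = 0.3 percentage points, so a group shift is not detected beyond chance. Repeat simulations gave 5.3% to 5.6% for a 2 SD shift and 1.9% to 2.2% for opposite responses. The last row shows that Friedman does its own job, the time effect.

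**Step 4: separate tests in each group.** If two independent tests each reject with probability p, they disagree with probability 2p(1−p). With an identical +0.6 response, p was about 0.485, giving 2 × 0.485 × 0.515 = 0.50; a direct count gave 52%, and the excess over the ceiling of 50% is simulation error. For a response of 0.8, p was about 0.74, giving 2 × 0.74 × 0.26 = 0.38; direct counts were 39-40%.

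**Step 5: change scores as a substitute.** Suppose both groups respond by the same factor, e^0.8 = 2.23, so the raw change is 1.23 times the resting value. If one group rests 1 log unit higher (2.72-fold), its raw changes are 2.72 times larger although the log-ratio is 0.8 in both. In simulation, Mann-Whitney on raw change rejected in about 5%, 20% and 50% of runs for resting differences of 0, 1 and 2 log units, with no difference in log-scale response.

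**The case against.** The strongest reply is about scope. Skewed outcomes go to transformation first, and those that transform keep the full mixed ANOVA. A reader might infer that all skewed outcomes lose the patient-control comparison, or that cytokines, microparticles and secretory IgA will do so. The article supports neither: it does not say which outcomes, if any, will fail transformation. This stands and limits the point.

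The simulated data are also log-normal. They would become normal on the log scale and never reach Friedman. The Friedman rates are unaffected by that, because ranks do not change under a monotone transformation. The comparator rates, however, do not describe data that truly resist transformation, such as values piled up at a detection limit. The loss on such outcomes is not quantified. Steps 1 and 2 do not rely on the simulation.

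A reader might also take the 40-50% disagreement as the plan's false-claim rate. It is not. The article does not say that Friedman will be run group by group, or that differing significance will be read as a group difference. The figure only shows why that reading would be unsafe.

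Finally, this is a non-randomised feasibility study whose analysis is meant to generate hypotheses, and Friedman validly tests the time effect within a group. That lowers the seriousness.

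Two defences do not succeed. The matter is not simply left to a fuller document, since the article names a specific test as the alternative and that test does not fit the design. Nor does the text confine Friedman to the time effect or pair it with a between-group test.

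**Conclusion.** The point holds for outcomes that remain non-normal after transformation. For these, two of the three effects in the plan, group and group-by-time interaction, have no test. That follows from the ranking itself and needs no assumption. The sizes (about 5-6% rejection for a 2 SD group shift, about 2% for opposite 0.8 SD responses) rest on 15 per group, correlation 0.5 and the assumed response pattern. The wording should be fixed before analysis. It does not threaten the study: the fallback is conditional, and the article rests no confirmatory conclusion on it.

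**What to change.** Restrict Friedman's test to the time effect within a group. For group and interaction on outcomes that cannot be transformed, name a rank method that keeps the factorial structure, for example the Brunner-Langer ANOVA-type statistic for one between-participant and one within-participant factor. Its interaction is defined on distribution functions, not on mean changes, and the plan should say so.

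Mann-Whitney (two groups) or Kruskal-Wallis (more than two) may be used on pre-exercise values for the resting difference. If either is applied to change scores, the scale should be prespecified and justified, for example a log-ratio instead of a raw difference, because raw change can show a false interaction when resting levels differ. The plan should add that differing significance in separate within-group tests is not evidence of a group difference.

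The cost is one or two sentences of analysis wording, with no new data and no change to design or sample size.
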